### Ethical Considerations

The trial will be conducted in accordance with the requirements documented in the latest version of the Declaration of Helsinki (Helsinki, 2024) and with the Standards of Good Clinical Practice. The trial is authorized for conduct by the Galician (Spain) Committee on Ethics in Medicines Research with code 2025/043 and by the Spanish Agency for Medicines and Medical Devices. It also has the agreement of the participating centers. This trial has been registered in the European Clinical Trials Register under EUDRACT code 2024-518936-36-00.

The researchers at each center will provide each participant with a patient information sheet, approved by the clinical research ethics committee, informing them about relevant study data and requesting access to their clinical and personal data recorded in their medical history and disclosed during visits. Permission is also requested for tests, examinations, and questionnaires, and the patient is informed that these actions are part of their daily clinical practice. In addition, the researcher will verbally inform the patient about the trial and answer their questions to ensure they understand the implications of their participation. The patient will be informed of their right to withdraw consent at any time and their right to have their data deleted. The patient will be informed of the possibility of being withdrawn from the study for safety reasons (an adverse event caused by the study medication) or for failure to comply with established procedures.

No patient may be included who has not given written informed consent to participate in the trial. Secondary analyses using existing data are included in the primary consent and do not require additional consent.

The research team and the sponsor of this study expressly undertake not to disclose the identity of the patients treated and to respect the confidentiality rules regarding the data and information to which they have access by participating in the trial.

In order to guarantee the confidentiality of the trial data, only the sponsor and members of the research team, the Research Ethics Committee for Medicinal Products, and the relevant health authorities will have access to them.

The research team undertakes to collect, record, and report the data accurately and correctly. The sponsor and the research team guarantee the confidentiality of the participants’ data and will ensure compliance at all times with the provisions of EU (European Union) Regulation 2016/679 of the European Parliament and of the Council of 27 April 2016 on the protection of natural persons with regard to the processing of personal data and on the free movement of such data (General Data Protection Regulation), and Organic Law 3/2018, of 5 December, on the Protection of Personal Data and Guarantee of Digital Rights.

Patients will be identified by a number in the database that guarantees complete data confidentiality, particularly the participants’ identity. Data will be sent to the study sponsor in pseudonymous form so that it is not possible to identify the patient in any way. The trial guarantees that patients cannot be identified in any of the images or supplementary material in the manuscripts obtained after this clinical trial. All information obtained as a result of this study will be considered confidential. The investigator may only report on the development and results of the study to the sponsor, the ethics committee, and the relevant health authorities.

The participant will not receive any remuneration for participating in this trial. Expenses incurred during visits related to the study will also not be covered.

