**Methods:**

A prospective, multicenter, open-label, controlled, parallel, phase IV clinical trial of 402 smoker patients prepared to quit smoking. The study was conducted in 10 hospitals in Spain. A control group is compared to 2 intervention groups in which the duration of the drug is increased without increasing its dose, administering half and all, respectively, of an additional marketed container that includes 100 tablets. Thus, participants will be randomized to three groups in a 1:1:1 ratio to receive cytisinicline: (1) a control group treated with cytisinicline according to the usual clinical guidelines and product information (25 days); (2) a group with a 50-day cytisinicline regimen (an additional 25 days at a dose of 1.5 mg every 12 hours), seeking to increase its efficacy while minimally impacting adherence; and (3) a group with a 75-day regimen (an additional 50 days at a dose of 1.5 mg every 12 hours), attempting to increase its efficacy, although the longer duration of the drug may threaten adherence. Efficacy in the 3 arms will be analyzed through sustained abstinence at 6 and 12 months, point abstinence rate assessed every 7 days, and abstinence rate from Day 25 to Day 50 and from Day 25 to Day 75 in the 3 study arms. (1) The variation in withdrawal and craving symptoms in the 3 groups, (2) safety through the percentage of adverse events in the 3 treatment arms, and (3) economic impact by evaluating the cost-effectiveness and cost-utility ratios of the 2 prolonged regimens versus the usual clinical cytisinicline regimen. To calculate the differences between the 3 groups for each outcome variable, a univariate analysis will be performed. Statistically significant variables will be included in a multivariate model.

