### Criteria for Discontinuation of Treatment/Intervention

A patient will be withdrawn from the study when the investigator becomes aware that a participant is experiencing a serious or intolerable adverse event that prevents continuation of the drug study.

The patient may also be excluded from the study at the investigator’s request (eg, if the investigator believes that the participant’s health could be compromised by continued treatment with the study drug). Noncompliance is not grounds for discontinuing treatment.

If a patient becomes pregnant during the study treatment period, treatment with the study drug must be discontinued. However, the participant must remain in the study to continue with safety and other study assessments.

Discontinuation may also occur at the participant’s request if they do not wish to continue drug treatment.

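### The article gives two rules on noncompliance that do not agree; with an undefined analysis population, withdrawing non-compliers could bias the 75-day comparison, in a direction that depends on how they are counted

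*Protocol article*

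**What the plan says.** Criteria for Discontinuation of Treatment/Intervention states: "Noncompliance is not grounds for discontinuing treatment". The same section does not keep stopping the drug apart from leaving the study. Under a heading about treatment it opens with "A patient will be withdrawn from the study when the investigator becomes aware" (of a serious or intolerable adverse event), and it then allows exclusion from the study at the investigator's request. Staying in the study after stopping the drug is spelled out only for pregnancy: "However, the participant must remain in the study to continue with safety and other study assessments".

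Ethical Considerations describes what participants are told: "The patient will be informed of the possibility of being withdrawn from the study for safety reasons", and the sentence ends "or for failure to comply with established procedures". The article does not say which procedures are meant.

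Three other places bear on the consequence:

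- Population of Analysis places efficacy and safety in the clinically evaluable population and does not define it.
- The abstract's Methods paragraph describes the 50-day arm as "seeking to increase its efficacy while minimally impacting adherence", and says of the 75-day arm "although the longer duration of the drug may threaten adherence".
- Patient Enrollment and Randomization confirms that there is no blinding, and Trial Monitoring leaves monitoring to each site's own investigators or a delegate.

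**The concern.** Consider a patient in Arm C who stops the maintenance tablets on day 35. Under the discontinuation section, a site would have no ground to act and would go on following the patient. Under the wording in Ethical Considerations, another site could withdraw the same patient from the study, which also ends treatment. The arm is known when that choice is made, and the article describes no central check that would make sites apply one rule.

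Reduced adherence is a possible cost of longer treatment and so part of what the trial should measure. If non-compliers are withdrawn more often in one arm and are then left out of the analysis, the randomised comparison becomes partly a comparison of adherers. The planned evaluation of how adherence affects cost-effectiveness and cost-utility (Specific Outcomes, Economic Evaluation) would also lose some of the patients it needs.

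**Working it through.** **Do the two statements collide?** The first concerns stopping treatment and the second leaving the study. Leaving the study before day 25, 50 or 75 (by arm) entails stopping treatment, so over that period applying the second does what the first rules out. After the last tablet there is no treatment to stop and the wording no longer collides. The possibility of study withdrawal remains, however, and the main abstinence outcomes at 6 and 12 months fall in that later period.

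**Figures in the plan.** The point rests on no stated figure. For scale, Sample Size Determination assumes 30% abstinence with 25 days and 50% with 75 days, a contrast of 20 points. A three-group chi-square test at 30/45/50%, alpha 0.05 and power 80% needs 109 per arm, against the stated 110. Then 110 × 1.21 = 133.1, rounded to 134, and 134 × 3 = 402, as stated. The 21% loss rate is a single figure, not split by arm.

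**Illustration of bias.** Inputs:

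- True abstinence p = 30% in every arm, which is the plan's control rate with no regimen effect.
- Share withdrawn for noncompliance, w. This is assumed, because the documents give none.
- Abstinence among those withdrawn, q = 0, 10 or 20%. This is also assumed.

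Formulas for the observed rate:

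- withdrawn patients leave the denominator: (p − wq)/(1 − w)
- withdrawn patients are kept and counted as smokers: p − wq

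Worked case with w = 5% in A and 25% in C, and q = 20%. Removed: A = (0.30 − 0.01)/0.95 = 30.5%, C = (0.30 − 0.05)/0.75 = 33.3%, difference +2.8 points. Counted as smokers: A = 29%, C = 25%, difference −4 points.

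| Withdrawn A / C | q | A, removed | C, removed | C − A, removed | C − A, counted as smokers |
|---|---|---|---|---|---|
| 5% / 15% | 0% | 31.6% | 35.3% | +3.7 | 0 |
| 5% / 15% | 10% | 31.1% | 33.5% | +2.5 | −1 |
| 5% / 15% | 20% | 30.5% | 31.8% | +1.2 | −2 |
| 5% / 25% | 0% | 31.6% | 40.0% | +8.4 | 0 |
| 5% / 25% | 10% | 31.1% | 36.7% | +5.6 | −2 |
| 5% / 25% | 20% | 30.5% | 33.3% | +2.8 | −4 |
| 10% / 30% | 0% | 33.3% | 42.9% | +9.5 | 0 |
| 10% / 30% | 10% | 32.2% | 38.6% | +6.3 | −2 |
| 10% / 30% | 20% | 31.1% | 34.3% | +3.2 | −4 |

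With equal withdrawal in all arms (15% or 21%) and the same q, C − A is 0 under removal. If everyone is followed and analysed with the true outcome, all arms stay at 30%.

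**Chance of a false positive.** Under removal, with 134(1 − w) patients per arm and a two-sided 5% test of C against A, the chance of a significant result favouring C runs from 4% (5%/15%, q = 20%) to 30% (10%/30%, q = 0). The nominal value in that direction is 2.5%.

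**The case against.** The strongest reply is that the two sections address different things. The discontinuation section is the operational one and deals with treatment. Ethical Considerations reports only a possibility mentioned to patients, and established procedures may mean visits, co-oximetry and tests rather than tablets. Much of the article also suggests that non-adherers and smokers are meant to be followed: adherence is measured and enters the economic evaluation, relapse is counted to 6 and 12 months, and care is described for participants who finish without quitting. Table 1 lists not smoking under recommendations.

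This stands in part. It makes withdrawal for smoking alone an unlikely reading, and it narrows the conflict. It does not remove the conflict, because the procedures are undefined, the discontinuation section itself mixes leaving the study with stopping the drug, and the patient-facing wording permits withdrawal from the study.

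A reader might go further and infer that the longer regimens will look better. The documents do not support that. It would need more withdrawals in the longer arms, lower abstinence among those withdrawn, and their removal from the denominator. The abstract gives the first only as a risk, and only for the 75-day arm; it expects little effect on adherence at 50 days. The second is stated nowhere. The third is permitted by an undefined population but not stated, and the definition may sit in an analysis plan that is not shown.

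**Conclusion.** The inconsistency is real and should be removed. Its effect on the result is possible rather than established, and its direction is open. Under the assumed unequal withdrawal (5–10% in Arm A, 15–30% in Arm C) and a true difference of zero, the 75-day arm gains about 1 to 10 points if non-compliers leave the denominator. The upper end is about half of the 20-point contrast on which the trial is sized (9.5/20). The effect is null or reversed, 0 to −4 points, if they are counted as smokers. There is no bias if withdrawal is equal across arms and they leave the denominator. These ranges also assume that abstinence among those withdrawn is the same in each arm. None of the withdrawal shares comes from the documents, so no single figure should be quoted as the expected bias.

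**What to change.** Reconcile Criteria for Discontinuation of Treatment/Intervention, Ethical Considerations and the patient information sheet so that one rule on noncompliance applies at all sites, and say what established procedures covers. Which treatment-stopping rule to keep is for the sponsor.

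Whichever rule is kept, add that noncompliance does not by itself end outcome follow-up, and that these patients stay in the efficacy comparison in their randomised arm. Amend Population of Analysis to match.

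The cost is a sentence or two in the protocol and matching wording in the information sheet. The Results section says that the first preselected patients are about to have their initial visit, so the change is best made now. Abstinence rates in the longer arms may look slightly less favourable than they would with non-compliers left out.

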## Results

Trial recruitment and patient registration will conclude in November 2026. Follow-up for all participants will continue until December 2027. At the time of this writing, we have 12 preselected patients at the sponsoring center (Smoking Unit, University Hospital Complex of Santiago de Compostela, Spain) who meet the exclusion and inclusion criteria of the study and who will begin the initial visit in the coming days.

## Discussion

### Principal Findings

Extended treatment regimens with cytisinicline of 50 and 75 days may be more effective than the 25-day treatment regimen currently used in clinical practice. Furthermore, the percentage of adverse effects and the economic cost should not be higher with extended treatment regimens. These expected results will confirm the current scientific evidence on this drug. For example, a multicenter observational study conducted in Spain with more than 300 patients treated with cytisinicline for 25 days shows a relapse rate of 20% in the 2 months following the end of treatment. For every point increase in craving at the end of treatment, the success rate of smoking cessation decreases by 13% at 6 months of follow-up [25]. In other words, the intensity of craving at 4 weeks is inversely correlated with the drug’s efficacy. Increasing the number of days of drug administration could correct this intense desire to smoke.

Two placebo-controlled clinical trials conducted in the United States compared a cytisinicline regimen at a dose of 3 mg every 8 hours for 6 weeks versus 12 weeks. These trials showed an increase in the number of smokers who quit smoking when the treatment regimen was extended beyond 6 weeks. Furthermore, the increased number of treatment days allowed a group of smokers who were gradually reducing their consumption to quit smoking, thus increasing the percentage of smokers who quit. In other words, there will be a group of smokers who will require a longer time to quit smoking [21,22]. No greater number of adverse events were observed with these prolonged regimens. In Europe, a clinical trial in a lung cancer screening program demonstrated that a prolonged cytisinicline regimen with doses different from those specified in the product information—an 84-day regimen—was more effective than the 40-day regimen, without a greater number of side effects [23].

As strengths, it is the first study to compare 3 different cytisinicline regimens: a standard 25-day regimen used in routine clinical practice approved in the product information versus 2 prolonged treatments of double and triple duration without modifying the dose or frequency of the same, unlike other studies that evaluate a higher dose, a different frequency of administration, or compare cytisinicline with other drugs [21-23].

This is a low-intervention study due to several characteristics: (1) studies of extended regimens exist in the European Union [23]. These analyze the efficacy and safety of extended cytisinicline treatments of 40 and 84 days. We also have experience with extended doses of 1.5 mg every 12 hours for 3 months [24]; (2) modifications to drug administration are minimal. One of the study arms corresponds to the regimen used in daily clinical practice; and (3) patient selection was performed according to the drug’s prescribing information. All of this ensures its feasibility.

Unlike other studies that propose a substantial change in the dose and frequency of the molecule, this one uses extended treatment regimens of an additional 25 and 50 days, with minimal modification to the commercially available drug formulation. Thus, in Spain, each pack of cytisinicline contains 100 tablets, so one-third of patients will be randomized to take half the tablets contained in the additional pack (2 tablets a day for an additional 25 days) and another third to take all of them in that pack (2 tablets a day for an additional 50 days). Furthermore, these regimens, with their lower administration frequency, could be more adherent than regimens of 3 times a day for 12 weeks.

At the time of this writing in Europe, the same dose and duration of cytisine are used for all smokers. However, smokers represent a heterogeneous patient population with differences in dependence, emotionality, motivation, and comorbidities. This study, using a multivariate model, allows the identification of the group of patients who would require extended treatment with cytisinicline, personalizing its use in routine practice.

It is a multicenter study conducted in different geographical areas of Spain, with a representative sample. Moreover, it is carried out by a research group with experience in the diagnosis and treatment of smoking cessation. Patients treated in 10 specialized smoking cessation units accredited by scientific societies are included. Furthermore, this is an independent trial, free from the financial interests of the pharmaceutical industry, which enhances the rigor of the results. Funding for disseminating the results will be obtained through grants or public funds.

This trial incorporates the calculation of the economic impact of extended doses, determining the savings for the National Health System that these regimens could generate by increasing the number of ex-smokers.

The results of the study will be published in indexed scientific journals and presented at national and international conferences.

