### Eligibility Criteria

Male and female smokers over the age of 18 years who have smoked more than 10 cigarettes per day during the past year and during the month before the screening visit are eligible to participate in the study. Smokers must also be prepared and motivated to quit smoking (score of 7 or higher on the visual analog scale of motivation). Smokers who have received pharmacological treatment for nicotine dependence (nicotine replacement therapy, varenicline, bupropion, or cytisinicline) within the previous 3 months are excluded from participating in the clinical trial.

In addition, exclusion criteria (Textbox 1) have been designed, taking into account the considerations of the drug label. All patients meeting all inclusion criteria and no exclusion criteria are consecutively invited to participate until the calculated sample size is obtained in each center.

Exclusion criteria for the study.Renal and/or hepatic insufficiency.Over 65 years of age (due to limited clinical experience).Hypersensitivity to the active substance or to any of the excipients.Unstable angina.Recent personal history of acute myocardial infarction or recent stroke (less than 8 weeks).Clinically relevant arrhythmias or uncontrolled hypertension.History of psychiatric illness with and without treatment (panic disorder, psychosis, bipolar disorder, and depression) within the last 12 months.History of alcohol or other drug abuse within the last 12 months.Use of tobacco products other than cigarettes, e-cigarettes, or marijuana in the past month and did not agree to abstain from using these products during study participation.Patients being treated with antituberculosis drugs.Patients being treated with drugs metabolized by CYP1A1 (cytochrome *P* 450 family 1, subfamily A, polypeptide 1) and CYP1A2 (cytochrome *P* 450 family 1, subfamily A, polypeptide 2), especially those with a narrow therapeutic margin (eg, theophylline, tacrine, clozapine, and ropinirole).Pregnant or breastfeeding smokers.Women on systemic hormonal contraceptives.

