### Specific Outcomes Efficacy

Different outcomes will be used to measure the efficacy of cytisine in each arm of the clinical trial.

The sustained abstinence rate will be determined in each of the three treatment arms at 6 and 12 months, based on carbon monoxide co-oximetry results in ppm. The correlation between the sustained abstinence rate in each of the three arms studied at 6 and 12 months, based on co-oximetry results, and the self-reported abstinence at 6 and 12 months will be calculated.

Additionally, point abstinence will be analyzed every 7 days in each of the 3 arms studied, based on the results obtained in the CO tests.

The percentage increase in abstinence rates will be compared with the increase in the duration of cytisinicline use. The number needed to quit smoking for one patient in each treatment group will also be calculated.

Interval abstinence will also be determined in this clinical trial. The abstinence rate will be analyzed from Day 25 to Day 50 in all 3 study groups and from Day 25 to Day 75 in all 3 study arms. The abstinence rate will also be determined from Day 25 (usual arm), Day 50 (extended arm 1), and Day 75 (extended arm 2) up to 6 and 12 months.

Relapse rates will be analyzed in each treatment arm. The frequency and percentage of relapses will be determined in those who quit smoking from Day 25 (usual arm), Day 50 (extended arm 1), and Day 75 (extended arm 2) up to 6 and 12 months in all 3 arms.

Craving and withdrawal symptoms will be assessed during the clinical trial. The mean Minnesota Nicotine Withdrawal Scale (MNWS) score and the mean craving score will be calculated at the initial in-person visit in all 3 arms, and their change from this visit will be measured on days 25, 50, and 75 in all 3 study arms.

Predictors of continued abstinence at 6 and 12 months of treatment and of relapse (clinical, anthropometric, demographic, and smoking-related variables) will be determined in all study arms.

Quality of life in each group will be calculated using the EQ-5D-5L scale score at baseline, 50 days, 90 days, 6 months, and 1 year.

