### Efficacy Analysis

To determine the main objective of the work, the efficacy variable will be constructed as a dichotomous variable, resulting from an algorithm that will be constructed for this purpose once all the data from the study have been obtained. To study the causality between efficacy and treatment prolongation, a multivariate logistic regression will be constructed. To determine candidate variables, candidate variables will first be tested in a univariate regression. Those variables whose statistical significance has a *P* value of <.20 will become part of a multivariate model. The model that best explains causality will be determined using a measure of relative statistical model quality, the Akaike information criterion. The risk measure to be calculated is the relative risk with its 95% CI. Interim follow-up assessments will be analyzed using a survival analysis to determine the duration of abstinence after the smoking cessation date.

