### Conclusions

Cytisinicline, when used in a standard regimen, triples the likelihood of smoking cessation, as it is a well-tolerated drug with high adherence. However, the percentage of smokers who quit is less than 50%. Therefore, it is essential to design new administration methods and therapeutic regimens.

An optimization strategy for this drug, such as increasing its duration, enhances its benefits without compromising patient safety, representing a new opportunity for smokers to quit.

Furthermore, this study identifies the population of smokers susceptible to a prolonged treatment regimen with cytisinicline. All of this will lead to a reduction in the number of smokers, decreasing, in the short to medium term, morbidity, mortality, and the direct and indirect costs associated with smoking.

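### The Discussion says the trial identifies which smokers need extended treatment, but the analyses described find predictors of quitting, not of gain from extension

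*Protocol article*

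**What the plan says.** The claim appears twice in the Discussion. Under Principal Findings: "This study, using a multivariate model, allows the identification of the group of patients who would require extended treatment with cytisinicline", with personalised use in routine practice given as the result. Under Conclusions: "this study identifies the population of smokers susceptible to a prolonged treatment regimen with cytisinicline".

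The planned analyses are in the Methods. Specific Outcomes Efficacy lists "Predictors of continued abstinence at 6 and 12 months of treatment and of relapse", drawn from clinical, anthropometric, demographic and smoking-related variables, and adds that these "will be determined in all study arms". Efficacy Analysis describes the model: "To study the causality between efficacy and treatment prolongation, a multivariate logistic regression will be constructed". On covariates it says "candidate variables will first be tested in a univariate regression" and then "Those variables whose statistical significance has a *P* value of <.20 will become part of a multivariate model". The final model is chosen by the Akaike information criterion, and the effect measure is the relative risk with its 95% CI.

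Objectives names efficacy, safety and economic impact by regimen. It does not list finding the patients who benefit from a longer course. Sample Size Determination addresses the comparison of arms only.

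**The concern.** Saying who would require extended treatment is a statement about effect modification: for which patients is the difference between 50 or 75 days and 25 days larger? A predictor of abstinence answers another question, namely which patients are more likely to quit. The two can diverge in both directions. A strong predictor of quitting can go with much the same gain from extension at all its levels. A factor that changes the gain can show no overall association with quitting.

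This is more than a missing detail. The article makes a positive claim, attributes it to a particular model, and describes an outcome and a selection rule for that model that do not support the claim. If the predictor list were read as the Discussion suggests, longer treatment could be linked to patients who would have quit on 25 days, and patients with a real differential gain could be missed.

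**Working it through.** **1. What each section asks.**
- Principal Findings and Conclusions: who needs, or is susceptible to, extension. This is a between-arm difference that varies by patient type.
- Specific Outcomes Efficacy: what predicts abstinence and relapse. This is a level, not a difference between regimens.
- Efficacy Analysis: covariates enter by association with the outcome, then the Akaike criterion. This selects on level.
- Specific Outcomes (Economic Evaluation): predictors of abstinence are related to cost-effectiveness and cost-utility in the three arms. This is the nearest item, but it concerns cost ratios, not efficacy gain.

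No section contrasts the efficacy gain across patient types.

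**2. The plan's own sample size.** Inputs from Sample Size Determination: 30%, 45% (the bracket beside it says .40) and 50%, 80% power, 5% significance, 110 per arm. A three-group chi-square test on 2 degrees of freedom with 30/45/50% gives 109 per arm, which agrees with 110 (power at 110 is 80.7%). With 40% in the middle arm it gives 116. The trial is therefore sized for the overall arm comparison. The 402 randomised make 402/3 = 134 per arm.

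**3. What a model without interaction terms picks up.** Simulation with assumed inputs: 25 versus 75 days, 110 per arm, a binary factor split 50/50, 2,000 runs, tests at .05.
- *Prognostic factor only* (odds ratio 2.5, no interaction on the logit scale). Abstinence is about 21% to 39% at one level and 40% to 61% at the other, so gains are 17 and 21 points. The factor is significant in 91% of models without interaction; the interaction test flags it in 5%.
- *Effect modifier with no average association* (log odds ratio for the factor −0.6 on 25 days and +0.6 on 75 days). Abstinence is about 37% to 43% at one level and 24% to 57% at the other, so gains are 6 and 33 points. The factor is significant in 5% of models without interaction; the interaction test flags it in 56%.

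A variable with no average association passes a P<.20 screen about one time in five. If the univariate screen pools the arms, a modifier of the second kind would usually be dropped before the multivariate step.

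**4. Power if interactions were fitted.** Assumptions, not in the documents: one binary factor split 50/50, 30% on 25 days in both halves, and gains of 25 and 5 points. The average gain is 15 points, matching the plan's 30% to 45%.

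SE = sqrt[Σ p(1−p)/n] over four cells with rates .30, .55, .30 and .35.

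Σ p(1−p) = .2100 + .2475 + .2100 + .2275 = .895.

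- 110 per arm (55 per cell): SE = sqrt(.895/55) = .128; z = .20/.128 = 1.57; power = Φ(1.57 − 1.96) ≈ 35%.
- 134 per arm (67 per cell): SE = sqrt(.895/67) = .116; z = 1.73; power ≈ 41%.
- Difference in gains needed for 80% power: 2.8 × SE = 36 points at 110 per arm and 32 points at 134.

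Sensitivity for 25 versus 75 days at 110 per arm, 20-point average gain, same 50/50 split:

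| Gains (points) | Power, risk difference | Power, logit |
|---|---|---|
| 25 v 15 | 12% | 11% |
| 30 v 10 | 35% | 30% |
| 35 v 5 | 66% | 57% |
| 40 v 0 | 90% | 82% |

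For 30 v 10, 80% power needs about 354 per arm, or 354/110 = 3.2 times the plan.

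**The case against.** **The analysis plan may add interactions.** Efficacy Analysis neither states nor excludes arm-by-factor terms, and such detail is often left to a document that is not shown. This stands as far as it goes. A reader might infer that the model is confirmed to be main-effects only; the article does not say so. What remains is the mismatch between a stated claim and the analysis offered for it. Step 4 shows that unseen interaction terms would still not justify an unqualified claim of identification.

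**This is Discussion wording, not an objective.** True, and the primary arm comparison is untouched. But the Conclusions present it as something the study does.

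**Predictors are related to between-arm quantities in the economic evaluation.** Partly true, since Economic Impact Analysis defines its ratios as incremental. That does not address differential efficacy.

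**Predictors may be sought arm by arm.** The wording allows this reading. Even so, a predictor that is significant in one arm and not in another is not a test that the benefit differs.

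**Scale.** A reader might infer that a prognostic factor never bears on who benefits. That is too strong. A factor that multiplies quitting by the same ratio in every arm leaves the relative risk of extension unchanged but does alter the absolute gain. Whether benefit differs depends on the scale, so the scale has to be named.

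**Selection.** A reader might also infer that eligibility empties the claim by removing the variation it relies on. The documents do not support that as a separate fault. Limitations already says the participants do not represent smokers in general and that no evidence will arise for those over 65 or with serious psychiatric or cardiovascular disease. Dependence is measured by Fagerström score in those enrolled, and motivation still varies from 7 upward. At most, the text could add that motivation below 7 cannot be assessed.

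**Conclusion.** The point holds as a mismatch between claim and analysis. The Discussion attributes to the multivariate model the ability to identify who needs extended treatment. The analyses described yield prognostic factors for abstinence and relapse, and the outcome-based screen can remove a genuine effect modifier.

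Interaction terms would make the analysis relevant but not conclusive at this size: about 35% power at 110 per arm and 41% at 134 for gains of 25 versus 5 points. Power reaches 80% only when gains differ by roughly 32 to 36 points. These figures rest on assumed subgroup rates, a 50/50 factor and a single two-sided test at .05; a less even split gives lower power.

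The change should be made. It bears on a headline conclusion, not on the primary efficacy comparison.

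**What to change.** 1. In Principal Findings and Conclusions, replace the claim with wording such as: *the study will explore whether the benefit of extension differs by baseline characteristics*.
2. Describe the predictors in Specific Outcomes Efficacy as prognostic only.
3. For the exploratory aim, fit all arms in one model with arm-by-factor interactions for a short list fixed in advance, without the univariate screen. Candidates from Data Collection Variables and Table 3 are nicotine dependence, cigarettes per day, reward type and previous quit attempts. Table 3 shows reward at Visit 1 but has no Fagerström row, so confirm that dependence is recorded before treatment starts.
4. Report the extended-minus-standard difference in abstinence with its 95% CI at each level, state the effect scale on which interaction is judged, and label the results exploratory.
5. Optionally, note that motivation below 7 cannot be assessed.

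The cost is two reworded sentences, one extra analysis on variables the protocol already lists, and a less favourable claim. No additional patients or visits are needed. The Results section reports 12 preselected patients yet to have their initial visit, so on that account the list can be fixed before outcome data exist.
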